## Abstract

Background: About 287,000 women died globally during their pregnancy journey in 2020, yet most of these deaths could have been prevented. In Uganda, studies show that using Community Health Worker (CHW) visits to households with a pregnant woman can support the prevention of adverse maternal and neonatal outcomes. One such intervention is through the timed and targeted counselling (ttC) approach, where CHWs deliver tailored messages to mothers and their male caregivers at key stages of pregnancy. This study aims to evaluate the impact of the ttC approach on maternal health in Northern Uganda. The main outcomes include antenatal care attendance, advised place of delivery, and postnatal care visit. Methods: We will employ a cross-sectional quasi-experimental design, with retrospective data to compare an intervention group (where ttC is implemented) to a control group (without intervention) using the propensity score matching (PSM) technique applying a 1:1 ratio with a caliper width of 20% of the standard deviation to estimate the average treatment effects. Adjusted odds ratios after generating matched pairs will be reported with 95% confidence intervals with Rosenbaum sensitivity analysis carried out for robustness. Discussion: These findings can be used to modify the implementation of the ttC approach, thereby enhancing its efficiency and effectiveness.

## 1. Introduction

Maternal health refers to the health of women during pregnancy, childbirth, and the postnatal period. Each stage should be a positive experience, ensuring women and their infants reach their full potential for health and well-being [1]. About 287,000 women died during and following pregnancy and childbirth in 2020. Almost 95% of all these maternal deaths occurred in low and lower middle-income countries, and most could have been prevented [2].

Maternal mortality is a global challenge with 223 deaths occurring per 100,000 livebirths worldwide [3]. In Uganda, the maternal mortality rate is 336 deaths per 100,000 live births, which is higher than the UN’s target to reduce the global maternal mortality ratio to less than 70 per 100,000 live births [4,5]. Antenatal care (ANC) refers to the care given to pregnant women by skilled health care professionals (such as health education and promotion professionals) to ensure the best health conditions for both the mother and the baby during pregnancy [6]. This regular contact between the pregnant woman and skilled health care professionals at the health facilities is essential for the health of the women and their children [7].

However, the ANC attendance rate in Uganda is 59.9% for four or more visits [8]. This inadequate utilisation of ANC has been attributed to factors such as long wait times at health facilities, reliance on family or traditional healers for advice, and delayed initiation of care [9]. Compared with home birth, childbirth in a health facility attended by skilled birth attendants is associated with improved maternal and child health outcomes, including lower rates of maternal morbidity and mortality [10,11]. However, in Uganda, only 76.6% of pregnant women deliver in a health facility [12]. The choice for the advised place of delivery (PoD) is often influenced by factors such as social, cultural, and environmental factors [13]. However, regarding Uganda specifically, little is known about factors that influence the use of health facilities for delivery, especially in rural areas [13]. Unfortunately, in Uganda, the knowledge of professionals and policy makers regarding the uptake of early postnatal care (PNC) is also low, hindering the formulation of effective policies aimed at reducing maternal mortality [14]. The first 7 postnatal days account for approximately 65% of maternal deaths, with half (50%) of these deaths occurring within the first postnatal day [15]. However, in Uganda, only approximately 22.5% of new mothers attend at least one PNC visit within six weeks [12].

Studies in Uganda have shown that preventable maternal deaths can be averted by community health worker (CHW) visits to pregnancy households, which also plays a crucial role in improving overall ANC attendance, PoD, and PNC [16,17]. These CHWs use various training packages to effectively deliver messaging to pregnancy households, among which is the timed and targeted counselling (ttC) family-inclusive behavioural change communication approach that targets families expecting a child, especially those most vulnerable and marginalized [18]. The ttC CHWs are part of an already existing structure established by the government of Uganda that links village inhabitants to health units [19]. However, these ttC CHWs receive additional training using the ttC package, which differs from the normal Ugandan government’s training package, as it encourages more timely and targeted visits to pregnancy households with a prescribed message at certain points of the pregnancy [18]. The ttC-trained CHWs are expected to maintain up-to-date ttC registers, detailing records of all the new and existing pregnancy cases, number of visits, situation found at households visited, and to tailor their messages to each individual household’s situation to be more effective [18]. As soon as a pregnancy case occurs and is identified in their routine community visits, they concentrate the ttC intervention on this household by counselling them in order to influence their uptake of life-saving maternal health services such as ANC, PoD, and PNC at the health facilities [18,19]. They apply a dialogue counselling methodology with the pregnant women at the household level, based on the assessment of current needs and practices and the negotiation of progressive improvements. This approach encompasses a wide range of life-saving health practices through appropriately timed messages delivered through interactive storytelling. Importantly, the training package (ttC) seeks to engage both the mother and male caregiver (this should be the male in the household providing support and care to the mother throughout the whole pregnancy journey) as decision-makers, embracing a family-inclusive and gender-transformative model of child health and development in which the positive contribution of male caregivers is emphasized [18]. 

In Northern Uganda, the ttC package is currently implemented by CHWs, based on a facilitator’s manual. To simplify the ttC message, the CHWs use interactive stories to draw different scenarios of problems, best practices and possible solutions faced during and immediately after the pregnancy period. These messages are timed, given at specific intervals and targeted, in order for the message to come neither too early nor too late for the mother, throughout the pregnancy and the postnatal period, to effectively influence the decision making in the households both for the mother and their male caregivers [18].

In recent years, innovative studies have indicated that counselling improved maternal and neonatal health outcomes [20,21]. For example, in Italy, Burgio et al. provided evidence that counselling was effective in managing high-risk pregnancies, and beyond the childbirth period, reduced stress in both the mothers and the fathers [20]. Similarly, in Eastern Uganda, an intervention by CHWs was shown to significantly improve antenatal care attendances [22]. However, according to a WHO study, there is limited evidence-based evaluation knowledge on the impact of the available global training packages for CHWs reviewed including ttC that are designed to improve maternal health continuum of care [23]. This protocol therefore would like to bridge this gap by detailing a study on the impact of the ttC training approach by CHWs on the maternal health continuum of care outcomes in Northern Uganda. Our hypothesis is that ttC will impact the maternal health continuum of care outcomes in Northern Uganda. This hypothesis is based on the available literature that suggests that targeted counselling interventions can improve these outcomes [16,24]. We anticipate that the timely message provided through ttC will encourage women to attend ANC visits [18]. Additionally, the messages raising awareness about the importance of delivering at health facilities are expected to increase the proportion of women delivering at the advised PoD [18]. Furthermore, the ttC visits towards the birth of a child are expected to drive more mothers to go to the PNC visits [18].

### Conceptual Framework

The conceptual framework for this study is based on an adapted Andersen’s Behavioural Model (shown in Figure 1). It shows how maternal health behaviours are influenced by ttC in the presence of various factors proposed by Andersen’s model [25,26]. According to Andersen’s model, predisposing, enabling, and need-based factors affect maternal healthcare utilization [27]. In the current study, predisposing factors include social and demographic factors such as the mother’s age, education level, parity, and marital status. The enabling factors include income level of the household and male involvement in the pregnancy journey. The need-based factors are the presence of chronic illnesses, and psychological issues of the mother. While of importance to the study is the impact of ttC on maternal health behaviours, Andersen’s model helps us to account for how predisposing factors, enabling factors, and need-based factors shape healthcare utilisation. Secondarily, it contributes to understanding the contextual factors influencing maternal health outcomes, which supports efforts to address healthcare access inequality and inform policy development for more equitable access to care [25,26]. 

In this study, we shall incorporate Andersen’s model in investigating the impact of ttC (as an intervention) on ANC utilisation, PoD, and PNC. The ttC is hypothesised to influence maternal healthcare utilisation across the above three aspects by improving mothers’ knowledge on the benefits of fast and sufficient ANC visits, thus improving their attitudes towards ANC. ttC is also hypothesized to improve male-involvement, as well as enhancing the mother’s awareness of their health status and history, thereby affecting PoD and creating need for PNC.

**
General Objective
**

The main objective of this study will be to assess the impact of ttC on the maternal health continuum of care outcomes in Northern Uganda.

**
Specific Objectives
**

To investigate the impact of ttC on ANC utilisation among pregnant mothers.To evaluate the impact of ttC on the advised place of delivery among pregnant women.To assess the impact of ttC on PNC utilisation among mothers.

**
Hypotheses
**

The study will be guided by the following hypotheses:ttC implementation will lead to an increase in the utilisation of ANC among pregnant women.ttC will result in a greater proportion of pregnant women delivering at health facilities.ttC will lead to increased PNC utilisation among mothers.

## 2. Methods

### 2.1. Research Design

A cross-sectional quasi-experimental research design with retrospective data collection comparing the intervention group to the control group will be used. Because of the cross-sectional data collection, a randomised control trial is not an option and, therefore, propensity score matching will be used to improve causal inference in this experimental design, as has been used in other similar impact study settings [28,29,30]. PSM will match each treated unit with a nontreated unit of similar characteristics using propensity scores generated from chosen covariates. The preferred characteristics for matching so as to reduce bias and improve precision within the model in this study are education level, birth parity, income, and age of the participants [31]. 

### 2.2. Research Area

The study area will be the northern region of Uganda, specifically the Oyam district, which was selected because ttC is implemented in the Aber subcounty of the district. Northern Uganda in particular is an important region for studying maternal health due to its high poverty rates [32], cultural diversity, limited healthcare access, poor health outcomes, and the presence of conflict-affected individuals [33].

Taking the Oyam district as the sampling frame, two subcounties, Aber and Otwal, are chosen for reaching out to mothers who would have given birth within the past 2–12 months. Aber is the treatment subcounty, and Otwal is the control subcounty because ttC is implemented in the former, but not in the latter. However, the two subcounties of Aber and Otwal were chosen because they are located within the same district and therefore have similar health challenges, such as limited health care access and similar poverty situations in the conflict-affected region [33]. Approximately 18.3% of the population in Aber and 22.3% of the population in Otwal aged 10–19 years have ever been married [34]. Furthermore, in 2021, these two subcounties, among others in Oyam district, had one of the highest teenage pregnancy rates in Uganda [35,36]. Factors mentioned by these new young mothers for the high rate of teenage pregnancy include a lack of knowledge of the ovulation period, inadequate sex education, and social norms that prevent parents from talking to their children about sex education [36]. Significantly, both subcounties are chosen because they do not share borders with each other; thus, limited spillovers are expected from the treatment subcounty to the control subcounty.

### 2.3. ttC Intervention

This ttC package has been identified by WHO as the only available global CHW training package that has supporting material that guide country-specific integration, as opposed to other generic packages available that develop capacities of CHW in maternal health [23]. It targets the first 1000 days (pregnancy and postpartum) of a child’s life [18]. Before implementation of the ttC approach, the CHWs were first trained for 5 days using a standardised ttC package. This training was guided by a developed package that outlined the specific tasks CHWs should, the targeted messages to deliver, and the appropriate timing for these messages [18]. 

After training, the CHWs were then grouped and supervised administratively by district health officials who meet them on a monthly basis for support supervision and review of the ttC household register updates. CHWs then identified households with pregnant women or likely households with reproductive-aged women and encouraged them to register and notify the CHW as soon as a pregnancy case occurred [18].

When a pregnancy is identified by the CHW, they visit these households of the pregnant women in a timely manner during the pregnancy and postnatally, with targeted messages to encourage the pregnant women to attend ANC services and plan to give birth in the presence of skilled personnel and attend to PNC. They further encourage male caregivers to be involved in the whole cycle, from pregnancy through birth to nurturing the baby, by providing both emotional and logistical support. CHWs make four visits during pregnancy before birth and seven visits postnatally in the first 2 years after birth, as explained in Table 1, which summarizes and provides a concise and visually organized reference for the key components and objectives of the ttC approach, as adapted from the ttC manual [18]. 

#### CHW Service Delivery in the Control Subcounty

The CHW in the control subcounty did not follow the ttC approach, but followed the government of Uganda’s national guidelines for recruitment, training, and supervision of CHWs [37]. They were supposed to map out and visit households with pregnant women to ensure that these attended ANC visits and accessed other essential services, but without the timely delivery of targeted messages characteristic of the ttC intervention. They were required to update their CHW registers with progress, which was then reported to the district health officials for supervision. 

### 2.4. Study Population

The study population/sampling frame is composed of respondents at the household level who will be selected from two subcounties, one with mothers who have given birth between 2 and 12 months of age and who participated in the ttC model sessions (with 876 mothers in the treatment group forming part of the sampling frame), or mothers whose access to ttC sessions was limited to the other subcounty of interest (with 1355 mothers in the control group also forming part of the sampling frame). Thus, the total sampling frame/study population will have 2231 mothers from which the sample will be drawn. The mothers will be recruited from the CHW registers that show that they should have attended counselling sessions during their pregnancy. Inclusion criteria are that the mother had a baby between 2 and 12 months. All other mothers are excluded.

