### 2.8. Sampling Procedure

To reach the above calculated sample size, a three-stage sampling procedure will be used. First, a simple random sampling within Oyam district will be conducted to select one subcounty where the treatment (ttC implementation) was applied (Aber subcounty) and another where it was not (Otwal subcounty). This random selection ensured that both the intervention and the non-intervention areas were chosen in an unbiased manner.

In the second stage, stratified sampling will be done within the two subcounties to provide the sampling unit, being women of reproductive age (between 18 and 49 years) who have given birth to babies between 2 and 12 months of age. For internal homogeneity within each subcounty, two strata will be formed, one from each subcounty. A total of 930 mothers will be sampled from the 2231 eligible mothers (465 from the 876 available in the intervention subcounty and 465 from the 1355 available in the control subcounty) as per the sample size calculation above. 

Finally, in the third stage, a systematic sampling method will be applied to randomly select the 930 mothers from an alphabetically compiled list of eligible mothers. A random starting point and a fixed interval will be applied to select participants 465 participants from each subcounty. This process ensures an equal and unbiased representative sample for later generalisation of findings to other similar settings. The flow of this sampling process is shown in Figure 2 below.

By justifying and implementing this comprehensive sampling methodology, the study will aim to enhance the reliability and validity of the research findings.

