## 3. Discussion

This study protocol describes how the current study will evaluate the impact of the ttC model on the maternal health continuum of care outcomes in Northern Uganda using a cross-sectional quasi-experimental design and employing propensity score matching to control for selection bias [39]. This study will integrate Andersen’s behavioural model, which identifies predisposing, enabling and need-based factors, to obtain a comprehensive understanding of whether emphasizing these factors within the ttC model will result in a more effective maternal health continuum of care outcomes [26]. 

We expect that ttC will significantly improve the maternal health continuum of care outcomes ANC, PoD, and PNC. These outcomes are important to study because they have shown to improve the overall health and wellbeing of both the mother and the child, which reduces the infant and maternal mortality rates globally, thereby contributing to the achievement of Sustainable Development Goal 3 on health and well being [44,45]. Improved ANC utilisation has been linked to early identification of complications, and preventing maternal deaths and comorbid conditions like anaemia [45,46,47]. Ensuring that more women deliver at the advised PoD allows trained professionals to manage both anticipated and unanticipated complications that arise during delivery thereby preventing stillbirths and improving the survival rate of the newborns [48,49]. In addition, since the first days after birth are associated with the highest risks for both the mother and the baby, having PNC visits is essential for the prevention of infection and management of infectious diseases such as HIV and malaria, and maternal anaemia [50,51,52].

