11th visit at 18 months of life (PNC)	Giving three to four meals to the child a day, child sleeping under a mosquito bed net.

Note: CHW = community health worker, ANC = antenatal care, HIV = human immunodeficiency virus, AIDS = acquired immunodeficiency syndrome, STIs = sexually transmitted infections, PoD = advised place of delivery, PNC = early postnatal care, ttC = timed and targeted counselling.

**Table 2 mps-07-00098-t002:** Study variables and their definitions.

Variable	Definition of Variable	Answering Scale
Intervention Variable		
ttC	This is a behavioural change approach implemented through CHWs to pregnancy households with a wide range of life-saving health practices through appropriately timed messages delivered using interactive storytelling to improve maternal health service utilisation. Mothers will be asked whether they received ttC from a CHW during their pregnancy.	1 = Yes 0 = No
Outcome Variables		
ANC	This is defined as visits to skilled health personnel during pregnancy. Mothers will be asked whether they attended any ANC visits during pregnancy.	1 = Yes 0 = No
PoD	This refers to the advised place of delivery, in a health facility. Mothers will be asked where they gave birth, with answering options including private health facilities, government health facilities, traditional birth attendant’s homes, or their own homes.	1 = Yes 0 = No
PNC	This refers to the care given mothers immediately after birth. This includes at least one PNC visit within the first 6 weeks after delivery. Mothers will be asked whether they visited a health facility for PNC after delivery.	1 = Yes 0 = No
Independent Variables		
Predisposing Factors		
Age	Mothers will be asked for their age at their last birthday.	1 = <20 2 = 21–25 3 = 26–30 4 = 31–35 5 = 36–40 6 = >40
Education level	Mothers will be asked for the highest level of school ever attended.	1. Preschool 2. Primary 3. O Level 4. A level 5. Tertiary 6. University 7. Non
Parity	Mothers will be asked how many births they have had in their lifetime, including the most recent one.	
Marital status	Mothers will be asked for their current marital status.	1. Widowed 2. Married or living together 3. Divorced or separated 4. Never married or never living together
Enabling Factors		
Income level	This refers to the income of the household. Mothers will be asked, on average, what is their approximate maximum monthly.	1. <200,000 2. >200,000–<500,000 3. >500,000–<1,000,000 4. >1,000,000–<2,000,000

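### Eligibility is worded in two ways, and the formal criterion, read naturally, leaves out mothers whose baby was stillborn or died early

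*Protocol article*

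**What the plan says.** The protocol article describes who is eligible in three sections.

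- Section 2.2 (Research Area) counts from the delivery: "mothers who would have given birth within the past 2–12 months".
- Section 2.4 (Study Population) gives the 2 to 12 months as an age when it describes the frame, "mothers who have given birth between 2 and 12 months of age". It then states the only formal criterion: "Inclusion criteria are that the mother had a baby between 2 and 12 months. All other mothers are excluded".
- Section 2.8 (Sampling Procedure) defines the sampling unit as women "who have given birth to babies between 2 and 12 months of age".

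No section says how a stillbirth or an infant death is to be handled. The Discussion (section 3) credits delivery at the advised place with "preventing stillbirths and improving the survival rate of the newborns". Delivery at the advised place is one of the three main outcomes.

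**The concern.** A baby who was stillborn or died in the first weeks never reaches two months of age. A field team working from section 2.4 would therefore be likely to pass over a mother who delivered five months ago and lost her baby in the first week. A team working from section 2.2 would keep her. The two wordings enrol different women.

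What is at stake is more than wording. If place of delivery affects survival, as the Discussion says, then requiring a baby aged 2 to 12 months selects women partly on a consequence of a primary outcome. Table 1 suggests a second route: the fourth and fifth ttC visits cover newborn care and prompt response to danger signs, so ttC could change survival even among women with the same place of delivery. Propensity matching on education, parity, income and age balances the women who are sampled. It cannot bring back women whom the eligibility rule left out.

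**Working it through.** **The plan's own figure.** Section 2.7 gives P1 = 71.5% (control), P2 = 81.5% (ttC), P = 76.5%, critical values 1.96 and 0.842, a design effect of 1.5 and 10% nonresponse.

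- n = 2 × (1.96 + 0.842)² × 0.765 × 0.235 / 0.10² = 282.3
- 282.3 × 1.5 = 423.4, and 423.4 × 1.1 = 465.8

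This agrees with the stated 465 per group. The point below concerns who enters the denominators and leaves this figure alone.

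**Effect of the living-baby reading on facility delivery.** Let p be the true proportion delivering in a facility, and let f and h be the proportions of mothers left out (stillbirth, or death before two months) after facility and other delivery. Among the mothers kept, the proportion is

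p(1 − f) / [p(1 − f) + (1 − p)(1 − h)].

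The documents give neither f nor h, so all the values below are assumptions.

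| Pattern | Control f / h | ttC f / h | Control | ttC | Difference (points) | Odds ratio |
|---|---|---|---|---|---|---|
| No selection | 0 / 0 | 0 / 0 | 71.5% | 81.5% | 10.0 | 1.76 |
| (a) | 4% / 8% | 4% / 8% | 72.4% | 82.1% | 9.8 | 1.76 |
| (b) | 5% / 15% | 5% / 15% | 73.7% | 83.1% | 9.4 | 1.76 |
| (c) reversed | 8% / 4% | 8% / 4% | 70.6% | 80.9% | 10.2 | 1.76 |
| (d) ttC also lowers loss | 5% / 15% | 4% / 8% | 73.7% | 82.1% | 8.4 | 1.64 |

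Worked example, (b), control: 0.715 × 0.95 = 0.67925 and 0.285 × 0.85 = 0.24225, so 0.67925 / 0.92150 = 73.7%.

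Pattern (c) stands for a setting in which high-risk births are referred to facilities.

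**Why the odds ratio holds in (a) to (c).** Selection multiplies the odds in each arm by (1 − f)/(1 − h). With the same f and h in both arms the factor cancels, and (0.815/0.185)/(0.715/0.285) = 1.76 is unchanged. In (d) the factors differ: the odds are 0.67925/0.24225 = 2.804 in the control arm and 0.7824/0.1702 = 4.597 in the ttC arm, a ratio of 1.64.

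**Pattern (d) with no true effect on place of delivery** (71.5% in both arms): 73.7% against 72.4%, a difference of −1.4 points and an odds ratio of 2.618/2.804 = 0.93.

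**Share of deliveries left out.** In the control arm this is 0.715f + 0.285h: 5.1% in (a), 7.9% in (b) and 6.9% in (c).

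**The case against.** The strongest reply is that all three wordings are loose forms of one delivery window, which section 2.2 states outright. No section says in words that the baby must be alive. This stands as far as it goes: a reader might infer that bereaved mothers are definitely excluded, but the text supports that only as the natural reading of sections 2.4 and 2.8. It does not settle the matter, because the restrictive wording sits in the only formal criterion, together with an explicit exclusion of everyone else.

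A reader might also infer that these women are missing from the registers. The documents do not support that. Section 2.4 says "The mothers will be recruited from the CHW registers that show that they should have attended counselling sessions during their pregnancy", and nothing says that entries are removed after a loss. Nor is it stated whether the counts of 876 and 1355 include such mothers.

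A further tempting inference is that all three outcome rates are overstated and the contrast between arms always shrinks. That goes too far, for three reasons:

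- Pattern (c) reverses the direction.
- The abstract promises adjusted odds ratios, and for place of delivery these are unaffected if loss depends on place of delivery alone.
- Losses do not always follow the outcomes. A stillbirth before labour precedes delivery, and early deaths fall inside the PNC window, which Table 2 describes thus: "This includes at least one PNC visit within the first 6 weeks after delivery".

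The odds-ratio argument does not dispose of the point. The abstract and section 2.10 also promise average treatment effects, and a difference in proportions does move. If loss depends on place of delivery and ttC changes place of delivery, the odds ratios for ANC and PNC are not protected in general. No size was calculated for those two outcomes.

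The effect is also small against sampling error. With 465 per arm the standard error of the difference is √(2 × 0.765 × 0.235 / 465) = 2.8 points, or 3.4 after multiplying by √1.5. The largest shift in (a) to (c) is about 0.6 points. Finally, restricting the study to mothers of surviving infants would be a legitimate target, but the protocol would have to say so, and it does not.

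**Conclusion.** The concern holds in a limited form. Eligibility is stated inconsistently, and the formal criterion, read naturally, selects partly on a consequence of a primary outcome by the protocol's own account of what facility delivery does. Matching cannot undo this.

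The size rests wholly on assumed loss rates. If loss depends only on place of delivery, the planned 10-point difference becomes roughly 9.4 to 10.2 points and the odds ratio for place of delivery stays at 1.76. If ttC also improves survival within place of delivery, the illustration gives 8.4 points and 1.64. The documents do not support a claim of large bias or of bias in one known direction. The case for changing the text is that the conflict over who is enrolled is real and cheap to remove.

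**What to change.** Use one rule in sections 2.2, 2.4 and 2.8: any mother whose delivery, live birth or stillbirth, took place 2 to 12 months before interview, whether or not the baby survived. Because the lower limit is counted from delivery, the six-week PNC window is still complete for every woman. Draw the list from the CHW and ttC registers on that rule and recount the frame of 876 and 1355. Record the baby's status at interview, and report the analysis restricted to surviving babies as a sensitivity analysis.

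The cost is a change of wording, a recount from registers already in use, one added question and one added analysis. The small downside is that interviewers must be prepared to speak with bereaved mothers.
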